### Study endpoints

The primary endpoint is the prevalence of nasopharyngeal carriage of the newborn at the age of 6 days for any of the following bacteria: *S.aureus*, GBS and *S.pneumoniae*.

Secondary endpoints include:

- Prevalence of nasopharyngeal bacterial (*S.aureus*, GBS and *S.pneumoniae*) carriage of the newborn at different time-points during the first months of life.
- Prevalence of nasopharyngeal, vaginal and breast milk bacterial carriage (*S.aureus*, GBS and *S.pneumoniae*) of the mother at different time-points during the first month after delivery.
- Prevalence of non-susceptibility to macrolides among bacteria (*S.aureus*, GBS and *S. pneumoniae*) isolated from the clinical samples collected from the newborns and their mothers during the first month after delivery.
- Proportion of newborns with at least one episode of purulent conjunctivitis and ocular *C. trachomatis* infection within the first week of life, the first 4 weeks of life and during the 8 weeks of the follow-up period.

We also measured AZI concentrations in the breast milk of the first 40 women recruited into the trial at two time points during the first week of life. Other endpoints not initially included in the protocol are weight gain during the first 8 days of life and the time from BCG vaccination to the appearance of a scar.

As safety endpoints, we included the number of solicited and unsolicited AEs in mothers and newborns observed during the first 6 days after treatment; and number of AEs in mothers and newborns reported during the first 8 weeks after treatment.

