### Screening, recruitment and randomization

#### Screening

When women presented to the labour ward in labour, a study nurse confirmed she had signed consent and assessed the continued willingness of the women to participate in the study. Subsequently, eligibility was determined using the criteria detailed below.

- Inclusion criteria: Pregnant women in labour aged 18 to 45 years presenting to the JFPH for delivery
- Exclusion criteria
  - Known HIV infection
  - Any chronic or acute condition that might interfere with the study as judged by the research clinician
  - Planned travel out of the catchment area during the 2 months after delivery (follow-up period)
  - Planned caesarean section
  - Known required referral
  - Known multiple pregnancy
  - Known severe congenital malformation of the baby
  - Intrauterine death confirmed before randomization

- Known allergy to macrolides
- Intake of antibiotics in the week before randomization

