#### Referral procedures for SAE

Any AE for either a mother or a baby, was captured in the CRF. When a study baby visited JFPH with any illness or called the nursing team, s/he was initially seen by the nurse on duty who determined the need for the baby to be reviewed by the study physician at the health centre. If referral was needed, the clinician recorded and

instituted initial management of the child's condition before subsequently referring him/her to the MRC ward in Fajara or the Edward Francis Small Teaching Hospital (EFSTH) in Banjul. Study related procedures (such as daily/weekly visits) continued as per protocol.

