### **Statistical analysis**

A flow chart will be used to describe the number of mothers who were eligible, randomised and treated, and the number of samples obtained from mothers and children at each time point.

The adequacy of the randomisation procedure will be checked by comparing baseline characteristics of mothers (ethnicity, age, season enrolled, hours from treatment to delivery, mode of delivery, time to rupture of membrane, apgar score, multiple pregnancy) and newborns (sex, birth weight, gestational age) between arms. Some of these variables are measured post intervention, but are unlikely to be influenced by the intervention (time from treatment to delivery, mode of delivery, time to rupture of membrane, Apgar score). Prevalence of bacterial carriage in the mother pre-intervention will also be used to check comparability of baseline characteristics (NPS and vaginal swab).

The primary analysis will be based on intention to treat (ITT). We will include data on twins but will not adjust for the effect of clustering (the average cluster size will be close to 1 so the design effect will be negligible). A per protocol analysis will be conducted excluding samples from mothers who vomited less than 15 min after medication was taken, samples collected after the use of antibiotics, and samples arriving at the lab more than 8 h after collection.

The prevalence of bacterial carriage will be compared between arms at each time point (in NPS, vaginal swabs and breast milk). The prevalence of carriage will be presented separately for each species and combined (i.e., carriage of *S.aureus*, GBS or *S.pneumoniae*). In addition, carriage acquisition rates will be compared between arms for the periods 0–6 days and 7–28 days (acquisition will happen when a non-carrier will become carrier in the subsequent sample). Ratios of prevalence and 95 % confidence intervals will be calculated for each of these comparisons, and Fisher's exact test will be used to compute p-values for the comparisons of prevalence.

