A Poisson regression model will be used to assess the effect of the intervention on prevalence of carriage across all time points. The model will include time, baseline carriage status of the mother, mother's age, ethnicity, season, sex of the newborn, and gestational age. Robust standard errors will be used to account for the dependence between observations from the same individual as well as the model misspecification (carriage status is binary and therefore does not follow a Poisson distribution).

To calculate prevalence of carriage at day 3 and day 6 we will use data from samples (NPS newborns and mothers, breast milk) collected within 1 day of the scheduled visit. At 14 days we will use samples collected between 12 and 18 days, and at 28 days we will use samples collected between 25 and 31 days. For vaginal bacterial carriage at day 8–10 we will use samples collected between 7 and 13 days. Samples were not collected after children received antibiotics. Where a sample was collected in lieu of the missing sample (i.e., before antibiotics were given) this will be used in place of the missing sample, even if it was collected outside the appropriate window period.

We will present analyses based on the available data. For the primary outcome we will conduct two additional analyses using the ITT cohort. First, a subgroup analysis in women who gave birth 2 h or more after taking the drug. And second, a sensitivity analysis using multiple imputation of missing data. In the imputation model, bacterial carriage in missing samples will be imputed from data on bacterial carriage at other time points and baseline demographic data (age and ethnicity for mothers, and sex and birth weight for newborns).

Changes in prevalence of bacterial carriage over time will be plotted for NPS in mothers and newborns, and breast milk. The plots will include point-wise 95 % confidence intervals for each prevalence estimate.

The numbers and rates of adverse events, serious adverse events (overall and specifically with a diagnosis of neonatal sepsis), purulent conjunctivitis, Chlamydial conjunctivitis, and deaths in newborns will be reported by trial arm. Rates of adverse events and serious adverse events will be reported in mothers. Rates will be compared between trial arms using Poisson regression, and robust standard errors will be used to allow for heterogeneity in the rates between individuals.

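### The only mortality item compared by arm is death in newborns, so a fetal death after randomisation falls outside the death comparison, which conditions on live birth

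*Protocol*

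**What the plan says.** The Screening section enrols "Pregnant women in labour aged 18 to 45 years presenting to the JFPH for delivery". The only exclusion that concerns fetal death is "Intrauterine death confirmed before randomization". The drug is taken after enrolment, so the fetus is undelivered at dosing.

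Study endpoints defines safety for two groups, mothers and newborns. It includes the "number of AEs in mothers and newborns reported during the first 8 weeks after treatment".

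Statistical analysis sets out what is tabulated. For babies, after adverse and serious adverse events, it says "purulent conjunctivitis, Chlamydial conjunctivitis, and deaths in newborns will be reported by trial arm". For mothers it says "Rates of adverse events and serious adverse events will be reported in mothers". It then adds "Rates will be compared between trial arms using Poisson regression", with robust standard errors.

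Stillbirth, fetal death and perinatal death are not named as outcomes anywhere in the Protocol, and newborn is not defined. On capture, the section on referral procedures says "Any AE for either a mother or a baby, was captured in the CRF".

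**The concern.** For a drug given before birth, harm or benefit to the baby can appear before or after delivery. A death count that starts at live birth selects its population on something that happens after randomisation and that treatment could in principle affect. If treatment moved deaths from the first days of life into labour, the newborn count would fall and look like benefit with no baby saved. A shift the other way would look like harm.

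Safety in mothers and newborns is a stated aim of the trial. The Discussion names neonatal sepsis and mortality as the targets of the next study if this one succeeds, so the death table is likely to be read as evidence for that step.

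**Working it through.** **No figure of the plan is in dispute.** The point rests on reading the sections together; the arithmetic only gives scale.

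**Step 1: can a fetal death occur in a randomised pregnancy?** Yes. Entry is in labour, and only a death confirmed before randomisation excludes. A fetus that dies between dose and delivery, or whose death is recognised only later, belongs to a randomised woman. The interval is not trivial by the Protocol's own account: hours from treatment to delivery is a listed variable, and a subgroup of women who delivered 2 h or more after the dose is planned.

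**Step 2: which tabulated item would count it?**

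| Item in Statistical analysis | Does a stillbirth after randomisation enter? |
|---|---|
| Deaths in newborns | No, on the ordinary meaning of newborn |
| Adverse and serious adverse events in newborns | Not stated; a stillborn baby has no follow-up time after birth |
| Adverse and serious adverse events in mothers | Possibly, as one event among all the others; not stated |
| Flow chart | No; it counts mothers eligible, randomised and treated, and samples, but not live births |

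No item shows it as a death by arm.

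**Step 3: scale, on assumed rates.** The documents give no rate of stillbirth or newborn death. Assume s = 0.5%, 1% or 2% of the 830 randomised women have a stillbirth after randomisation:

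- 830 × 0.005 = 4.2
- 830 × 0.01 = 8.3
- 830 × 0.02 = 16.6

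That is about 4 to 17 in both arms together, or about 2 to 8 per arm of 415. Let d be the assumed proportion of live-born babies who die. The share of all deaths that a newborn-only count leaves out is s / (s + d(1 − s)):

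- s = 0.5%, d = 2%: 0.005 / (0.005 + 0.02 × 0.995) = 0.20
- s = 1%, d = 1%: 0.01 / (0.01 + 0.01 × 0.99) = 0.50
- s = 2%, d = 0.5%: 0.02 / (0.02 + 0.005 × 0.98) = 0.80

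**Step 4: illustration of the distortion (invented counts).** Suppose each arm has 12 deaths among 415 fetuses. One arm has 8 stillbirths and 4 newborn deaths; the other has 4 and 8. Newborn deaths per live birth are 4/407 = 1.0% and 8/411 = 1.9%, which looks like a halving. All deaths are 12/415 in both arms.

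**Step 5: how much could the added rows show?** Little by way of testing. With 415 per arm and Fisher's exact test at an assumed two-sided 0.05, power to detect a doubling is about 5% from a base of 0.5%, 14% from 1% and 33% from 2%. A split of 4 against 8 gives p = 0.38. The rows are descriptive.

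**The case against.** The strongest reply is that this argues from silence. No section excludes stillbirths or restricts an analysis to live births, newborn is undefined, and a statistical analysis plan that is not shown may code the event and fix the denominator. Several provisions would also catch it: the safety window runs from treatment rather than birth, adverse events are recorded on day 0 before and after the intervention, those in mother or baby go on the case report form, and the local safety monitor and safety board review all serious events. Mortality is only a safety item in a proof-of-concept trial. The exclusions for known referral, multiple pregnancy, severe malformation and interfering conditions should lower the event rate.

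Most of this stands, and it limits the point. A reader might infer that stillbirths go unrecorded or are removed from the trial. The documents do not support that: a stillbirth would probably be captured as a serious adverse event. A reader might also take 4 to 17 as an estimate of lost deaths, but it is arithmetic on an assumed rate.

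What does not stand is that the matter is merely left open. Statistical analysis is not silent on mortality: it names the item and confines it to newborns. A stillbirth pooled with all maternal serious events is recorded but is not visible as a death by arm. If the analysis plan already defines the item more widely, the Protocol's sentence should be brought into line.

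**Conclusion.** The point holds in a limited form. As written, the only mortality comparison by arm is of deaths in newborns, in a trial that doses before birth and excludes only a fetal death already confirmed. That comparison conditions on live birth, and a fetal death after randomisation does not enter it. This rests on the ordinary meaning of newborn.

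The size cannot be known from the documents. On assumed rates of 0.5% to 2% for both stillbirth and newborn death, a newborn-only count would omit roughly 20% to 80% of deaths after randomisation; the numbers are small in any case. The primary carriage endpoint, its power and the sample size are untouched. The change is worth making because a few events can alter how a small death table reads, and because it costs almost nothing.

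**What to change.** In Statistical analysis, keep deaths in newborns and state that the item covers the full 8 weeks of follow-up. It should not be narrowed to neonatal deaths: the Background ends the neonatal period at day 28, so deaths from day 29 to week 8 would be lost. Add two rows by arm:

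- (a) stillbirths after randomisation;
- (b) stillbirths after randomisation plus newborn deaths through 8 weeks.

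Use all fetuses of randomised women as the denominator for both. Report counts, proportions and confidence intervals as descriptive safety results, without a testing claim. State also under whom a stillbirth is coded in serious adverse event reporting, so that it is handled alike in both arms.

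A separate line for fetuses judged already dead at randomisation should be added only if fetal status was recorded at the time. No section shows that it was, and recruitment has finished.

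The cost is two table rows. Study nurses were present around delivery and adverse events in mother and baby were captured, so the delivery outcome should already be available. Data cleaning was still under way at submission and the code is broken only after database lock, so the rows can be specified blind.

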## Methods/design

### Study objectives

The primary objective of the trial is to determine the impact of one oral dose of 2 g of AZI, given during labour, on the newborn's nasopharyngeal bacterial carriage at the age of 6 days for at least one of three pathogens: *S.aureus*, GBS and *S. pneumoniae*.

Secondary objectives are to determine the impact of the intervention on bacterial carriage in the nasopharynx of the baby, and in the vaginal tract and breast milk of the mother at different time points within the first 4 weeks after delivery. The impact of AZI on purulent conjunctivitis and ocular *C. trachomatis* infection will also be assessed.

To evaluate the safety of the intervention on mothers and newborns we monitored and assessed adverse events (AE). Special attention was paid to hypertrophic pyloric stenosis (HPS) in the newborn which is usually reported as projectile vomiting.

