### **Sample size rationale**

The original sample size (415 mother/baby pairs per arm) assumed a 15 % loss to follow-up (i.e. 353 participants in each arm for whom the primary endpoint is recorded). Based on data from a previous study [32], bacterial carriage (*S.aureus*, GBS or *S.pneumoniae*) on day 6 was assumed to be 60 % in the control arm. According to these assumptions, the study has 98 % power to detect a 25 % reduction in bacterial carriage (GBS, *S.pneumoniae* or *S.aureus*) and 88 % power to detect a 20 % reduction.

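### The rule for comparing event rates (Poisson regression with robust standard errors) has no exception for an arm with zero events, where its Wald test gives spurious extreme significance

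*Protocol*

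**What the plan says.** The Statistical analysis section names the outcomes to be reported by arm. For newborns they include "serious adverse events (overall and specifically with a diagnosis of neonatal sepsis") and "purulent conjunctivitis, Chlamydial conjunctivitis, and deaths in newborns will be reported by trial arm". Adverse and serious adverse events in mothers are added. The method follows directly: "Rates will be compared between trial arms using Poisson regression, and robust standard errors will be used to allow for heterogeneity". No exception, zero-cell rule or exact alternative is attached.

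The only exact method in the protocol belongs to a different family of comparisons. For bacterial carriage, Fisher's "exact test will be used to compute p-values for the comparisons of prevalence". Carriage is expected to be common: Sample size rationale assumes 60% in the control arm.

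The conjunctivitis outcome is also a secondary endpoint. Study endpoints defines it as "Proportion of newborns with at least one episode of purulent conjunctivitis and ocular" *C. trachomatis* infection, over the first week, the first 4 weeks and all 8 weeks.

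**The concern.** The robust variance is there to handle heterogeneity between individuals, which suits adverse events that are frequent or recur. It relies on events being present in both arms. The same sentence also governs outcomes for which one arm could well be empty in a trial of 415 pairs per arm.

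With an empty arm, the fitted rate there tends to zero and so do its residuals. The sandwich estimator then treats that arm as known almost without error, while the estimated log rate ratio runs towards minus infinity. The quotient is a very large z statistic.

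At stake is a safety table in which one death, or one chlamydial eye infection, against none carries a p-value that looks like proof of harm or benefit. The Discussion says a successful trial leads to studies of neonatal sepsis and mortality, so these lines will be read with interest.

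**Working it through.** **Inputs.** 415 pairs per arm, 1:1 allocation (Sample size rationale; Trial design). The method is from Statistical analysis. The protocol gives no expected number of deaths, sepsis cases or chlamydial cases, so event counts below are assumptions shown over a range. Equal follow-up and at most one event per child are also assumed.

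**The plan's own figures.** None is given for this analysis. The sample-size figures do reproduce: 415 × 0.85 = 352.75, or 353. At two-sided 5% (assumed), power is 98.0% for 60% v 45% (stated 98%). For 60% v 48% it is 89.4%, or 87.9% with continuity correction (stated 88%).

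**Why the standard error does not grow.** For an arm of n children with fitted mean μ, the robust variance of its log rate is Σ(y − μ)² / (nμ)².

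- Arm with b events, μ = b/n: the sum is b(1 − b/n), so the variance is 1/b − 1/n.
- Empty arm, every y = 0 and μ → 0: the sum is nμ², so the variance is 1/n, however small μ becomes.
- Total: 1/b − 1/n + 1/n = 1/b, so SE = 1/√b.

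The model-based variance is 1/b + 1/(nμ), which grows without limit as μ → 0. So it is the robust variance that produces the false significance.

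**Numerical check.** Poisson model, log link, arm as the only covariate, 415 v 415, heteroscedasticity-consistent (HC0) variance. The software reported convergence each time.

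| Events | Log rate ratio | Robust SE | Robust Wald p | Model-based Wald p | Fisher p | Conditional exact Poisson p |
|---|---|---|---|---|---|---|
| 0 v 1 | −20.4 | 1.00 | 2e-92 | 0.999 | 1.00 | 1.00 |
| 0 v 2 | −20.4 | 0.71 | 9e-183 | 0.999 | 0.50 | 0.50 |
| 0 v 3 | −21.4 | 0.58 | 2e-300 | 0.999 | 0.25 | 0.25 |
| 0 v 5 | −21.4 | 0.45 | below machine precision | 0.999 | 0.062 | 0.0625 |

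The size of the log rate ratio, and so of p, is set by the convergence tolerance. At a loose tolerance of 1e-4, 0 v 3 still gives p = 4e-102. With 353 per arm, 0 v 1 again gives 2e-92.

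**Intervals.** For 0 v 1 the robust 95% CI for the rate ratio is about 2e-10 to 1e-8. The exact conditional interval runs from 0 to 0.975/0.025 = 39.

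**How often an arm is empty.** With equal true rates and m expected events per arm, q = (1 − m/415)^415 is the chance that a given arm is empty. The chance of exactly one empty arm is 2q(1 − q). The last column enumerates binomial counts and counts every one-empty-arm table as a rejection by the robust test.

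| m | Exactly one empty arm | Robust Wald rejections at 5% |
|---|---|---|
| 0.5 | 47.7% | 47.7% |
| 1 | 46.5% | 46.5% |
| 2 | 23.3% | 23.4% |
| 3 | 9.4% | 9.8% |
| 4 | 3.5% | 4.6% |
| 5 | 1.3% | 3.1% |

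Up to m = 3 the rejections are almost entirely the zero-cell tables.

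**Both arms non-zero.** 1 v 7: robust p = 0.068, Fisher 0.069. 1 v 8: 0.049 against 0.038. The method is acceptable here.

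**The case against.** The strongest reply has four parts.

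*A zero-cell fallback is ordinary SAP content, and the SAP is not at hand.* Its absence alone would be no finding. But the protocol goes further than naming a default: it fixes this method for these outcomes without exception, and followed as written it gives a wrong result with an empty arm.

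*The failure would be seen.* Numbers and rates are reported by arm, so 0 v 1 would stand beside the p-value. The local safety monitor and the DSMB reviewed serious adverse events during the trial, and the protocol ties no monitoring decision to this regression. This stands and lowers the severity. It does not supply a valid comparison.

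*The condition may never arise.* Also fair: no event rates are given, and from about 4 expected events per arm the problem largely disappears.

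*The text does not specify a Wald test.* True. A likelihood-ratio test stays finite: for 0 v 1 the statistic is 2 × ln 2 = 1.39, p about 0.24. But it makes no use of the robust standard errors that the plan calls for, and it is liberal at small counts (0 v 3: 6 × ln 2 = 4.16, p about 0.04, against Fisher 0.25).

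A reader might also infer more than the documents support:

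- That hypertrophic pyloric stenosis is tested this way. Study objectives says "Special attention was paid to hypertrophic pyloric stenosis (HPS) in the newborn", but that is surveillance. The comparison paragraph does not single it out; it enters only among adverse or serious adverse events.
- That the method gives false reassurance. Every failure shown here is a false alarm or an unusable estimate.
- That model-based Poisson regression fails equally. Its Wald test is uninformative (p about 0.999), not falsely significant.

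**Conclusion.** The point holds as a conditional one. When exactly one arm has no events, the prescribed robust Wald comparison is invalid: it reports overwhelming significance from as little as one event or, in software that fails or drops the term, gives no usable estimate. In the former case the direction and size of the error do not depend on assumed event rates.

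How often this would happen does. The figures of about 46%, 23%, 9% and 4% at 1, 2, 3 and 4 expected events per arm rest on equal true rates, equal follow-up and one event per child at most. They are the probability of an empty arm, and so an upper bound on false positives from zero cells. They should not be read as the trial's established type I error, because the protocol gives no expected counts and some software would return no result.

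The exposure is limited to the rarest safety outcomes and the ocular *C. trachomatis* part of one secondary endpoint. The primary endpoint is unaffected, and comparisons with events in both arms behave acceptably. Severity: minor to moderate.

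**What to change.** Add one sentence after the Poisson regression rule in Statistical analysis. Suggested wording: *When either arm has zero events, the arms will be compared by Fisher's exact test on participants with at least one event, or by a conditional exact Poisson test, with an exact 95% confidence interval; Poisson regression with robust standard errors will be used otherwise.*

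Fisher's test on participants is the safer choice where one child can have repeated episodes, because the conditional Poisson test treats events as independent. A wider threshold, such as fewer than 5 participants with the event in either arm, is optional; the calculations support only the zero-cell rule.

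The cost is slightly more conservative inference for very rare events. Fisher's test rejects in about 0.04%, 0.5% and 1.2% of trials under no effect at 1, 2 and 3 expected events per arm, and with an empty arm it first reaches 5% at 0 v 6 (p = 0.031). No data collection changes. Trial status reports that laboratory work and data cleaning were still under way, and Blinding and Un-blinding says the code is broken only after database lock. On those statements, the wording can be settled before unblinding.
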